### Data collection and management

2.8

We will code the identification of patients. We will also enter data collected at each study visit into a paper CRF with double data entry. Outcome data entered into the database will be verified against the source data on the paper CRFs.

We will encourage patients to complete study and follow-up using text messages and personal calls.

### Sample size calculation

2.9

Preliminary studies of prospective observational studies require more than 12 participants.^[14,15]^ We calculated the number of patients needed considering the percentage of eligible patients who visit You & Green Korean Medicine Clinic on typical days; the estimated sample size was 40 participants. We will recruit 50 patients considering the dropout rate of 20%.

### Statistical analysis

2.10

We will analyze categorical and continuous variables with McNemar test and a paired *t* test (in the case of a nonnormal distribution, the Wilcoxon signed rank test will be used), respectively. We will also perform a Chi-squared test or a Fisher exact test for AE rates, the rates of AEs that cause dropout, and the rated of severe AEs.

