### Study design/setting

2.2

This study is a prospective multicenter observational study. We will recruit patients from the You & Green Korean Medical Clinic in 4 regions (Daejeon, Busan, Daegu, Sejong) (Fig. 1). Data collection and follow-up schedules are shown in Table 1.

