### Recruitment

2.5

We will recruit 50 female patients with infertility at the You & Green Korean Medical Clinic. The researcher will explain the aim of this study and the details of the procedures and will obtain informed consent from potential subjects prior to the collection of information. Participants will be free to withdraw at any time during the study, and this will not affect their clinical treatment.

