### Intervention

2.6

The participants will be treated for 3 months with the standard protocol practiced at the You & Green Korean Medical Clinics. KM interventions (herbal medicine, acupuncture, electroacupuncture, herbal acupuncture, auricular acupuncture, moxibustion, manual therapy, etc) will be prescribed for infertility treatment in the same manner as in actual clinical practice, without the limitation of the number of interventional treatments. Herbal medicine will be prescribed according to individual symptoms and pattern identification. The detailed herbal prescriptions according to pattern identification are listed in Table 2. The dosages and contents of the herbs will be the same as that used in actual clinical practice. If necessary, acupuncture or another KM will be prescribed once a week. If the patient becomes pregnant during treatment, these treatments will be stopped.

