#### Secondary outcome

2.7.2

Ovarian function testing: Ovarian function testing will be assessed with luteinizing hormone, follicle-stimulating hormone, estradiol, and AMH testing^[13]^ before and after the 3 months of KM treatments. Blood tests will be performed on the 2nd or 3rd day after the menstrual period.

Adverse events: All participants will be required to report any adverse events (AEs) when they occur during the trial at every visit. Each AE will be recorded in the case report form (CRF) by the site investigator and will be assessed for causality.

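### The adverse-event rates are assigned a chi-squared or Fisher exact test, but the study has one treated cohort and no comparison is named

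*Protocol article*

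**What the plan says.** Section 2.10 (Statistical analysis) of the protocol article has two parts. Categorical and continuous outcomes are compared within patients, by McNemar test and by paired t test or Wilcoxon signed rank test. AEs are then given a different kind of test: "We will also perform a Chi-squared test or a Fisher exact test for AE rates", and the sentence goes on to AEs leading to dropout and severe AEs. It names no groups, reference rate or hypothesis.

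The design sections describe one group:

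- Section 2.2: "This study is a prospective multicenter observational study". Recruitment is from clinics in four regions.
- Section 2.5: "We will recruit 50 female patients with infertility at the You & Green Korean Medical Clinic". No allocation or control is mentioned.
- Section 2.6: "The participants will be treated for 3 months with the standard protocol practiced at the You & Green Korean Medical Clinics".
- Section 2.9: "the estimated sample size was 40 participants", raised to 50 for dropout. This sizes a single cohort.

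AEs are a secondary outcome (section 2.7.2): "All participants will be required to report any adverse events (AEs) when they occur during the trial at every visit". Each one is recorded in the case report form and assessed for causality.

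**The concern.** Chi-squared and Fisher exact tests, as normally applied to event rates, compare independent groups. Every woman in this study receives Korean medicine, so the AE data form one row: women with an event and women without. The efficacy tests in the same section suit a one-group, before-and-after design. The AE sentence does not.

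This is more than a detail left to a fuller document. The article itself fixes a method, and the method does not match the design it describes. An analyst following the sentence must either set it aside or choose a grouping that the article does not name.

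The question of interest is how often AEs occur under this treatment and how precisely 50 women can show it. A test across, say, clinics asks instead whether the rate varies between clinics. A non-significant result there says nothing about whether the rate is low, yet it could be taken as reassurance. Section 2.10 names no other statistical analysis for AEs. The Discussion hopes that the results will help clinicians decide on this treatment, so an interpretable AE rate matters.

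**Working it through.** **Inputs from the article**

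- 40 participants needed, 20% dropout, 50 recruited (section 2.9).
- One treated population, no comparator (sections 2.2, 2.5, 2.6).
- Chi-squared or Fisher exact test for three AE rates (section 2.10).
- No expected AE rate is given, so every event count below is an assumption for illustration.

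**1. Reproduce the stated sample size**

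n = 40 / (1 − 0.20) = 50. This matches the article and confirms that a single cohort is sized. The AE test plays no part in it.

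**2. Apply the stated tests to the data the design yields**

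Suppose 5 of 50 women have an AE. The table has one row: 5 and 45.

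- Chi-squared: expected count = row total × column total / grand total, so 50 × 5 / 50 = 5 and 50 × 45 / 50 = 45. Observed equals expected, the statistic is 0, degrees of freedom = (1 − 1) × (2 − 1) = 0, and software returns p = 1.
- Fisher exact: with one row, only one table fits the margins. Its probability is 1, so p = 1.

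Both results hold for any number of events. The tests carry no information about the AE rate.

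**3. Look for another comparison in the article**

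- *Fixed reference rate.* A one-sample chi-squared goodness-of-fit test would need one, and none is stated. Fisher's test has no one-sample form.
- *Before versus after.* The article describes AE reporting during the study. A before-after comparison of the same women would be paired data, for which neither test is suited.
- *Subgroups.* The four clinics, the pattern-identification groups, and women with or without previous surgery are independent groups on which a test could be computed. Section 2.10 links none of them to AEs. If recruitment were even across the four regions (an assumption, as no site target is given), each would have 50 / 4 = 12.5 women on average.

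**4. What the cohort can show**

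Exact (Clopper-Pearson) 95% limits for x events in n women:

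- lower = 0.025 quantile of Beta(x, n − x + 1), taken as 0 when x = 0
- upper = 0.975 quantile of Beta(x + 1, n − x)

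For x = 0 the upper limit reduces to 1 − 0.025^(1/n) = 1 − 0.025^(1/50) = 0.0711.

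| Assumed events / treated | Proportion | Exact 95% interval |
|---|---|---|
| 0/50 | 0% | 0% to 7.1% |
| 2/50 | 4% | 0.5% to 13.7% |
| 5/50 | 10% | 3.3% to 21.8% |

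The denominator is 50 because a safety rate should count every woman treated, including those who later drop out. The figure of 40 is the number expected to remain after dropout. These intervals do not measure the error in the plan. They show the information that the stated test would leave unreported.

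**The case against.** The strongest reply is that the defect is an undefined comparison, not an impossible test. The article contains independent groups: clinics, herbal patterns and surgical history. Herbal prescriptions differ by pattern, so comparing AEs between prescriptions is a plausible intention. The section is very short, and the full protocol may name the groups.

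Part of this stands. A reader might infer that the test cannot be run at all. The documents do not support that, because it could be computed across one of those groupings. They support only that no comparison is defined. The reply does not rescue the sentence as the main safety analysis: even with groups supplied, the test would address differences between subgroups and would still not estimate the AE rate in treated women.

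A reader might also infer that no AE assessment exists before treatment. That cannot be confirmed, because the visit schedule (Table 1) and the flowchart (Figure 1) are not shown. The point does not depend on it, since neither test is a paired test.

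Finally, the harm is limited. AEs are secondary, the questionnaire and quality-of-life outcomes have their own paired analyses, no success criterion rests on the AE test, and the recorded data allow counts and proportions. The risk that a subgroup p-value is misread as reassurance is a possibility, not something the article proposes. The choice of exact interval is a reasonable convention, not the only valid one.

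**Conclusion.** The point holds in this form: section 2.10 assigns a between-group test to all three AE rates in a study with one treated cohort and no named comparison group, subgroup or reference rate. As written, the test has no defined comparison and cannot estimate AE risk. On the data as one row it gives p = 1 regardless of the events. Any other p-value would come from an unplanned split.

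Severity is moderate. A reader might infer that the safety evidence is lost or that the study as a whole is compromised. Neither follows: the AE data remain reportable, and the primary analyses and the target of 50 are untouched.

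The conclusion rests on reading the study as a single cohort, which sections 2.2, 2.5, 2.6 and 2.9 all support although the article does not use that term. The intervals also assume that all 50 recruited women start treatment, and that the event counts are illustrative.

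**What to change.** Replace the AE sentence in section 2.10 with wording such as: *For any AE, AEs leading to dropout and severe AEs, the number and proportion of participants with at least one such event will be reported with an exact (Clopper-Pearson) 95% confidence interval. The denominator is all participants who received at least one treatment. No between-group test forms part of the main safety analysis.*

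If a comparison between clinics or pattern groups is wanted, name the groups in advance and label it exploratory.

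The cost is one sentence of protocol wording. It needs no new data and no change to the sample size or to treatment.

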### Ethics and dissemination

2.11

The Institutional Review Board of Semyung University approved this study (SMU-IM-190501). Written informed consent will be obtained from all study participants prior to enrollment in the study (Supplement 1). The results will be published in a peer-reviewed journal and will be disseminated electronically and in print regardless of results.

## Discussion

3

This multicenter observational study was designed to investigate the effects of KM treatment on infertility caused by POR. All KM treatments will be delivered according to the patients’ symptoms and patterns. Although KM treatment or Chinese medicine treatment has been reported to increase the success rate of IVF,^[16,17]^ there is insufficient evidence that KM can improve POR-related infertility. The results of this study will provide us with more reliable research evidence and will provide a better scientific basis for clinicians to rationally choose KM in the treatment of infertile patients with low POR.

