### Study aims

2.1

The aim of this study is to investigate the effects of KM on poor ovarian reserve (POR) in infertility patients.

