#### Inclusion criteria

2.4.1

We will include patients who are eligible according to the following criteria:

1.Females between 25 and 44 years of age who have been diagnosed with infertility.2.Those without a history of surgical procedures but with an antral follicle count (AFC) < 4 or an anti-Müllerian hormone (AMH) level < 1.0 ng/mL in both ovaries confirmed through ultrasonographic examination.3.Those with a history of surgical procedures but with an AFC < 4 or an AMH level < 1.0 ng/mL in both ovaries confirmed using ultrasonography.^[11]^4.Failure to achieve a clinical pregnancy after 12 months or more (6 months for females aged 35 and above) of regular unprotected sexual intercourse.^[12]^5.Written informed consent to participate in the study.6.Compliance with the study regulations.

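### The single-arm before/after design can describe change in women receiving Korean medicine, but the aim and Discussion promise evidence of its effects and a basis for choosing it

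*Protocol article*

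**What the plan says.** - **Aim** (Study aims, 2.1): "The aim of this study is to investigate the effects of KM on poor ovarian reserve (POR) in infertility patients".
- **Design** (Study design/setting, 2.2): "This study is a prospective multicenter observational study".
- **Treatment** (Intervention, 2.6): "The participants will be treated for 3 months with the standard protocol practiced at the You & Green Korean Medical Clinics". The text describes no untreated or usual-care group.
- **Entry** (Inclusion criteria, 2.4.1): women without prior surgery qualify "with an antral follicle count (AFC) < 4 or an anti-Müllerian hormone (AMH) level < 1.0 ng/mL in both ovaries". The same cut-offs apply to women with prior surgery.
- **Outcomes** (2.7): the primary outcomes are a 44-item KM symptom questionnaire and the Korean EQ-5D. AMH is one of four hormones in a secondary outcome, measured "before and after the 3 months of KM treatments".
- **Analysis** (Statistical analysis, 2.10): McNemar test, and paired t or Wilcoxon signed rank test. Chi-squared and Fisher exact tests are named for adverse events only.
- **Sample size** (2.9): 40 women, set from patient flow, with the remark "Preliminary studies of prospective observational studies require more than 12 participants". With 20% dropout, 50 are recruited.
- **Planned inference** (Discussion): the results "will provide a better scientific basis for clinicians to rationally choose KM in the treatment of infertile patients". No caveat accompanies this.

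**The concern.** A paired test asks whether a measurement changed between two dates. The aim and the Discussion ask whether KM changed it. Without a comparator, an external benchmark or a stated limitation, nothing in the text connects the two questions.

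The gap opens by two routes:

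- **Primary outcomes.** Symptoms and quality of life are reported by women who sought care and know they are being treated. Natural course and expectation can produce improvement that the design cannot separate from a treatment effect.
- **AMH.** Women can be admitted because AMH is below 1.0 ng/mL, and AMH is then measured again. If the value that admitted a woman is also her baseline, the second value is expected to be higher even under an inert treatment.

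At stake is the published message. A significant before/after change could be offered to clinicians as grounds for choosing KM when it carries no information on whether KM caused it.

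**Working it through.** **The plan's own figure.** 40 / (1 − 0.20) = 50, so the recruitment target reproduces. The base of 40 comes from patient flow, with no effect size, SD or power, and cannot be re-derived.

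**Primary outcomes.** No arithmetic applies, because the article gives no expected change, SD or untreated course. The argument is structural: one treated group, self-reported outcomes, paired tests.

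**AMH: size of the artefact under zero effect.**

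Inputs from the article: entry cut-off 1.0 ng/mL, so c = ln(1.0) = 0; n = 40; paired t test. The two-sided 5% level is assumed.

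Further assumptions, none given in the article: log-AMH normal with SD s = 0.8 among attending women; median 0.8 to 1.5 ng/mL; test-retest correlation ρ = 0.7 to 0.9; the qualifying AMH is the baseline.

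Formulas, with μ = ln(median), a = (c − μ)/s and λ = φ(a)/Φ(a):

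- Expected log change: m = (1 − ρ) · s · λ
- Variance of change: v = (1 − ρ)² · s² · (1 − aλ − λ²) + s² · (1 − ρ²)
- Standardised change: d = m/√v. The rejection probability comes from the noncentral t with 39 df and noncentrality d√40.

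Worked case, median 1.0 and ρ = 0.8:

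- a = 0, λ = 0.798
- m = 0.2 × 0.8 × 0.798 = 0.128, and exp(0.128) = 1.136, a 13.6% rise
- v = 0.04 × 0.64 × (1 − 0.637) + 0.64 × 0.36 = 0.0093 + 0.2304 = 0.240, √v = 0.490
- d = 0.128/0.490 = 0.261, noncentrality 0.261 × 6.325 = 1.65, rejection about 36%

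If only 20 of the 40 enter on AMH and the other 20 show no AMH regression (change variance 2s²(1 − ρ) = 0.256):

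- mean change 0.064
- variance (0.240 + 0.256)/2 + 0.128²/4 = 0.252
- d = 0.127, rejection about 12%

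| Median (ng/mL) | ρ | Spurious rise, all on AMH | Rejection, all on AMH | Rejection, half on AMH |
|---|---|---|---|---|
| 0.8 | 0.9 | 5% | 14% | 7% |
| 1.0 | 0.8 | 14% | 36% | 12% |
| 1.5 | 0.8 | 20% | 64% | 20% |
| 1.5 | 0.7 | 32% | 83% | 28% |

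The nominal two-sided rate is 5%. Simulation from the same model agrees with these rates to within about one percentage point.

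**Is the AFC-only group a clean contrast?** Suppose women are split by qualifying AMH, and those at or above 1.0 ng/mL are reported separately. That group is truncated from below and regresses downward. At median 1.0 and ρ = 0.8 the case is symmetric: exp(−0.128) = 0.88, a spurious fall of about 12% (ignoring any AFC-AMH correlation).

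**The case against.** The strongest reply has four parts.

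1. **The baseline may already be separate.** Section 2.7.2 times the hormone tests to the menstrual cycle and places them before and after treatment. That fits a study draw distinct from the qualifying value. Section 2.4.1 gives no timing for the qualifying test, and the visit schedule (Table 1) is not shown. A separate draw would remove most of the AMH artefact. This stands. A reader might infer that regression to the mean will appear in this study; the document supports only that it can.
2. **The mechanism reaches a secondary outcome only.** Neither the symptom questionnaire nor EQ-5D is an entry criterion. This stands: the regression calculation says nothing about the primary outcomes. Their weakness is the missing comparator, and its size is unknown.
3. **Entry is by AFC or AMH.** The upper figures need all 40 women to qualify on AMH. The article does not give that share, so 83% is the top of an assumed range and no forecast.
4. **A single-arm observational study is legitimate.** The Introduction says it is meant to reflect actual practice, and section 2.9 refers to preliminary studies. This stands too. A reader might infer that the design is invalid or needs a control arm; for a descriptive purpose it does not.

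It can also be said that the closing Discussion sentence states expected value and is not a decision rule, and that section 2.11 commits to publication whatever the results. Both are true, but neither supplies the missing link. The sentence still says what the results will provide, and the aim still names effects.

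**Conclusion.** The concern holds in this form: the design can describe 3-month change in women receiving KM, and the aim and Discussion claim more than that. This rests on the text alone and needs no assumed figure. It applies to the primary outcomes and to AMH, by different routes.

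The AMH figures are conditional. If the qualifying value is the baseline, an inert treatment gives a significant paired test 14% to 83% of the time when all women enter on AMH, and about 7% to 28% when half do. Median, spread, test-retest correlation and the share entering on AMH are all assumed. If baseline is a separate draw, most of this disappears, but the claim about choosing KM remains unsupported.

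**What to change.** 1. **Reword the aim (2.1) and the Discussion.** Describe the 3-month change in symptoms, quality of life and ovarian function tests in women receiving KM. Call the results hypothesis-generating and not attributable to KM. Delete the statement that they give clinicians a basis for choosing it.
2. **Fix the AMH baseline in 2.7.2.** State that it is the study's own pre-treatment draw, separate from the value used to qualify. Where only the qualifying value exists, report regression to the mean as a limitation of the AMH result.
3. **Record on the CRF which criterion qualified each woman.** Do not present women with AMH at or above 1.0 ng/mL as a regression-free contrast. An adjustment for expected regression would also need a reliability figure that the article does not give.

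The cost is protocol wording, one CRF field and, where baseline AMH is now taken from the qualifying test, one further blood test. The claim becomes less favourable. Sample size and design are unchanged.
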